## Abstract

**Background:**

Major depressive disorders (MDD) are a debilitating and pervasive group of mental illnesses afflicting many millions of people resulting in the loss of 110 million working days and more than 2,500 suicides per annum. Adolescent MDD patients attending NHS clinics show high rates of recurrence into adult life. A meta-analysis of recent research shows that psychological treatments are not as efficacious as previously thought. Modest treatment outcomes of approximately 65% of cases responding suggest that aetiological and clinical heterogeneity may hamper the better use of existing therapies and discovery of more effective treatments. Information with respect to optimal treatment choice for individuals is lacking, with no validated biomarkers to aid therapeutic decision-making.

**Methods/Design:**

Magnetic resonance-Improving Mood with Psychoanalytic and Cognitive Therapies, the MR-IMPACT study, plans to identify brain regions implicated in the pathophysiology of depressions and examine whether there are specific behavioural or neural markers predicting remission and/or subsequent relapse in a subsample of depressed adolescents recruited to the IMPACT randomised controlled trial (Registration # ISRCTN83033550).

**Discussion:**

MR-IMPACT is an investigative biomarker component of the IMPACT pragmatic effectiveness trial. The aim of this investigation is to identify neural markers and regional indicators of the pathophysiology of and treatment response for MDD in adolescents. We anticipate that these data may enable more targeted treatment delivery by identifying those patients who may be optimal candidates for therapeutic response.

**Trial registration:**

Adjunctive study to IMPACT trial (Current Controlled Trials: ISRCTN83033550).

## Background

Major depressive disorders (MDD) are serious public and individual mental health illnesses predicted to be the leading health burden worldwide by 2030 [1]. First episodes of MDD often occur during childhood or adolescence, with additional episodes likely to recur in some 65% of cases [2,3]. Further to this, Harrington and Clark [4] report that childhood or adolescence onsets of affective disorder are evident in approximately 30% of adult cases. Adolescence can therefore be considered a critical period where the initial stages and trajectories of depression emerge [5]. Prior history of depression is associated with an increased risk of recurrence of MDD irrespective of concomitant level of prior or subsequent environmental adversity [6,7] indicating a key role for the illness per se in influencing natural history within individuals and making the delivery of effective treatment at the earliest stages of the illness highly important in relapse prevention.

Tackling this debilitating illness most effectively at the first emergence of an episode in adolescence could be seen as a crucial prevention strategy that may reduce the risk of recurrence of future episodes and prove integral for the long-term improvement of individual health outcomes. In this respect, structural and functional neuroimaging measures, either alone or in combination, have been used to identify brain areas indicative of efficacious treatment given in adulthood [8-10]; reviewed in [11,12]. Furthermore, structural and functional neuroimaging measures could have important prognostic clinical potential by identifying those individuals who are most likely to benefit from one or more forms of treatment [8,11].

### Treatments for MDD in adolescence

The United Kingdom (UK) National Institute for Health and Care Excellence (NICE) guidelines recommend a stepped-care approach for patients with MDD, where treatment options advance alongside escalating need for care. Although not always successful in leading to remission, provision of treatment, either in the form of psychotherapy, pharmacotherapy, or both, often is essential in order to interrupt the cycle of episodic relapse and recurrence in MDD. In adolescents with MDD, a form of psychotherapy such as cognitive behavioral therapy (CBT) is first provided which may or may not be accompanied by pharmacotherapy treatment with selective serotonergic reuptake inhibitors (SSRIs) such as fluoxetine (20 mg-60 mg).

A pragmatic randomised controlled superiority trial by our group compared SSRI and specialist clinical care (SCC) with a combined treatment regime of SCC + SSRI + CBT and showed that the addition of CBT was no more effective than SCC + SSRI at effecting remission by 28 weeks of treatment [13]. Although that study did not have a CBT-only or non-treatment control group, March and colleagues [14] noted that CBT alone was not superior to placebo in effecting remission by 12 weeks and both were less effective than fluoxetine alone or combination therapy.

### Brain imaging studies of MDD in adults

The IMPACT and MR-IMPACT research programmes aim to establish the extent to which psychotherapies with or without fluoxetine diminish the risk for relapse at 86 weeks after treatment and reveal neural regions or patterns of activity associated with treatment remission, recovery or relapse. A meta-analysis conducted by Fu and colleagues [11] compared neuroimaging evidence for volumetric and functional changes associated with symptom improvement following treatment (pharmacological, psychological, and combined approaches) for depression. Functional activity in bilateral regions of pregenual anterior cingulate cortex (pgACC) and right subgenual anterior cingulate cortex (sgACC)/medial orbitofrontal cortex (OFC) positively correlated with treatment response, with greater activity in those regions associated with an increased likelihood of responding to treatment for depression [11], mirroring findings from an earlier study [8]. A negative correlation between activation in right anterior insula and right putamen and treatment response also was observed [11]. Notably, a recent report by McGrath and colleagues [15] suggested that metabolic activity in right anterior insula could differentiate pharmacological versus psychological treatment response in patients with moderate to severe depression with the potential to optimize initial treatment selection in MDD.

In terms of brain structural predictors of treatment response, regional volume reductions in the right hippocampus, as determined through manual segmentation techniques, were associated with poorer response to treatment [11]. Although lacking sufficient power, reduced volume in bilateral dorsolateral prefrontal cortex (dlPFC), a region involved in the cognitive regulation of emotion, was associated with poorer response to treatment for depression. It is noteworthy that a recent meta-analysis of treatment effects in MDD observed across fMRI studies also identified bilateral dlPFC as a treatment-sensitive region [16]. Considered together, treatment response in MDD appears to be predicted by a number of key areas within the fronto-limbic network [17-19] including pgACC, sgACC, hippocampus, and prefrontal cortices. Increased activity in perigenual ACC (pgACC and sgACC regions) has been linked to successful treatment by pharmacological agents whereas decreased activity in this region has been linked to successful treatment by psychological therapy [8,9,20]; summarized in [12].

### Brain imaging studies of MDD in adolescence

Given the aberrant patterns of brain structure and function observed in adults with MDD, we can ask whether depression in adolescence is similar to depression in adulthood and whether common neural mechanisms underlie pharmacological and/or psychological effectiveness in spite of developmental processes occurring in the adolescent brain. Far fewer neuroimaging investigations of depression have been conducted in adolescents, with no single meta-analysis performed to our knowledge. Recent studies, however, suggest similar perturbations in brain structure and function in regions including, but not limited to, dlPFC, OFC, sgACC, and amygdala, irrespective of patient age [25-27]. Furthermore, fluoxetine may exert effects via common neural mechanisms in both adolescents and adults with MDD [26], and CBT treatment response was unaffected by age in a small group of adolescents with MDD [28]. These neuroimaging studies together suggest that MDD and effective treatment thereof may be instantiated by comparable mechanisms in adolescents and adults.

### Limitations of neuroimaging studies of MDD

There are, however, several limitations of previous neuroimaging research studies of MDD. Often mixed are cases that may represent distinct subtypes of MDD hence limiting the generalizability of findings. Furthermore, many treatment investigations of MDD have not examined treatment effects past 16 weeks, which is a relatively short time window considering that recovery may take up to 2 years in some cases [29], and that remission rates are 50% in first episode cases of clinic groups by 2 years [29]. Longitudinal investigations across the entire period of recovery are needed to understand why some individuals recover from MDD whereas others do not. The sample sizes of many neuroimaging studies are relatively small considering the substantial clinical heterogeneity across MDD cases. A failure to find statistically significant differences across the whole-brain may have prompted some studies to investigate case–control differences within hypothesis-driven regions of interest (ROI), which apply more lenient criteria for evaluating the statistical significance of results. When coupled with a relatively underpowered sample, inadvertent consequences of adopting ROI approaches are the potential to inflate Type I and Type II error rates due to the possibility of scanning an unrepresentative sample of MDD cases and a failure to include all regions where significant differences may occur across groups or conditions. Larger sample sizes permitting whole-brain examinations of volumetric and functional activation differences are therefore needed in order to better understand the pathophysiology of depression in adolescence.

### Aims

Neuroimaging examinations of adolescents with MDD provide an opportunity to reveal and differentiate pathophysiological and therapeutic neural structure and function between first episode sporadic as well as at risk recurrent forms of this disorder. Using a repeated-measures design in selected cases that have completed psychological treatment provides a longitudinal neuroimaging investigation of therapeutic effects that have the added potential of revealing neural sites that constitute state or trait markers of illness and treatment insensitivity.

MR-IMPACT will therefore examine neural markers of moderate to severe unipolar depression in adolescence and neurobiological predictors of recovery from depression. Specific objectives of MR-IMPACT are as follows:

• To define the profile of brain structural and functional differences in adolescent patients with depression at baseline compared to a group of healthy adolescent participants.

• To assess baseline measurements of brain structure, functional activation and connectivity, focusing on neural systems implicated in adult MDD (ACC and other fronto-limbic components) as predictors of symptomatic response to each of the three types of psychological treatments in the short-to-medium term (up to 86 weeks after the start of treatment).

• To measure changes in brain functional activation and connectivity before and after a course of CBT and development-related changes in brain function measured in a comparison group of healthy participants to permit identification of treatment-related changes in brain function.

## Methods/Design

### Study overview

MR-IMPACT is a pragmatic effectiveness trial of depression in adolescence. All adolescents enrolled in MR-IMPACT are simultaneously taking part in the Improving Mood with Psychoanalytic and Cognitive Therapies (IMPACT) trial [30], and have been randomly allocated to one of three forms of talking therapy (short-term psychoanalytic psychotherapy [STPP], SCC, and CBT; Figure 1). The IMPACT recruitment, baseline assessment and randomization procedures can be found together with the treatment protocol for each therapeutic arm in Goodyer et al. [30]. Another adjunct study of IMPACT, IMPACT-genes and hormones, will collect salivary cortisol pre- and post-therapy to assess HPA-axis functioning [30]. In adherence to UK NICE guidelines, patients allocated to any treatment arm may also be prescribed up to 50 mg of Fluoxetine for symptom reduction in the presenting episode.

**Figure 1 F1:**
[figure not shown]
The relation of the IMPACT trial to the MR-IMPACT study.

The study will be conducted in accordance with the Declaration of Helsinki [31].

### Study participants

The patient population will be recruited from a larger cohort of young people with depression who have agreed to take part in the IMPACT trial. All eligible and interested patients residing in London or Cambridgeshire will be invited to take part in MR-IMPACT, with enrolment targeted to reach 120 adolescents (male and female) aged 11 through 17 years who meet Diagnostic and Statistical Manual of Mental Disorders (DSM-IV) criteria for moderate to severe unipolar depression. Patients with chronic or recurrent MDD are also included, as are patients already taking antidepressant medication. A detailed list of the study exclusion criteria is provided below.

All patients will be provided an MR-IMPACT study information leaflet and will provide verbal consent to IMPACT research assistants to be contacted by telephone by an MR-IMPACT researcher a minimum of 48 hours later for potential participation in the MR-IMPACT study. Patients will be contacted to assess interest in and eligibility for the magnetic resonance imaging (MRI) scan. Patients with MRI contraindication will be ineligible and therefore excluded from the study at this point. For eligible patients, if the patient so chooses, one adult (typically a parent) may accompany the adolescent patient into the scanner suite. For the patients requesting this option, the identified adult will be screened over the telephone for MRI contraindications. Eligible patients will be scheduled for an MRI appointment where they are remunerated £30 for their time and inconvenience. Any fees incurred for travel to and from the MRI appointment will be reimbursed to the adult accompanying the patient.

A group of healthy control young persons matched for age, sex, intelligence quotient (IQ) and handedness will be recruited into the study for comparison. A letter will first be posted to all families with healthy adolescents who had participated in a previous study (i.e. the ROOTS study) [32]. The letter will describe the MR-IMPACT study and the current recruitment of siblings of ROOTS participants aged between 11 and 17 years, and request that interested families contact a member of the MR-IMPACT team to discuss participation and arrange a home visit. If needed, additional healthy control adolescents will be recruited from local schools within Cambridgeshire.

Prior to visiting the home, potential healthy control families will be posted MR-IMPACT study information sheets at least 48 hours in advance to allow ample time to consider study participation. At the home visit the study details will be reviewed prior to obtaining informed assent and consent by potential participants and their parent/caregiver, respectively. Screening for personal and family history of psychiatric illness and MRI contraindication will then be conducted. In a private setting, healthy adolescents will also be screened for history of attempted suicide, suicidal thoughts or cutting behaviour. After the home visit eligible healthy adolescents and their families will be contacted to arrange an MRI appointment at their convenience where adolescents will be given a stipend of £30 for their time and inconvenience. Any expenses incurred for travel to and from the MRI appointment will be reimbursed to the adult accompanying the healthy adolescent.

### Screening and MRI assessment

At the MRI assessment adolescents and their parents will be asked to review the study information sheet one final time prior to signing the MR-IMPACT study assent and consent forms. Adolescents will be re-screened for presence of MRI contraindication, as will any adults requested to accompany adolescents in the scanner suite. Adolescents will then be asked to complete the Edinburgh Handedness Inventory [33] and the Spielberger Trait Anxiety Inventory [34]. In preparation for the tasks the adolescent will be asked to complete in the MRI scanner, three similar tasks brief in length will be practiced on a computer in advance of the actual scan. The practice tasks will be administered in the same order as the MRI tasks are presented to minimise confusion. Patients will then be asked to complete the Spielberger State Anxiety Inventory [34] before attending the 1.5 hour MRI session. Upon completion of the MRI session, patients will be asked to complete the Bond-Lader Visual Analogue Scales [35] and then the Mood and Feelings Questionnaire-Short version [36]. Lastly, patients will be asked to complete two computerised tasks in follow-up to one of the completed fMRI tasks.

### Eligibility criteria

All patient participants will be required to meet DSM-IV criteria for moderate to severe MDD, as determined by child and parent interviews using the Kiddie Schedule for Affective Disorders and Schizophrenia-Present and Lifetime version (K-SADS-PL) [37]. A second criterion for inclusion within the IMPACT trial is a score of 27 or more on the self-report Moods and Feelings Questionnaire (MFQ).

### Inclusion criteria

1. Aged 11 through 17 years.

2. Current DSM-IV unipolar MDD diagnoses with moderate to severe impairment determined by child and parent interviews using the K-SADS-PL.

3. Score of 27 or more on the MFQ.

### Exclusion criteria

1. Alcohol dependence.

2. Drug dependence.

3. Pervasive developmental disorder or generalized learning problem.

4. Pregnancy or breastfeeding.

5. Concurrent medication use that could adversely interact with SSRIs.

6. MRI contraindication.

7. Brain abnormality.

8. Intolerance to the MRI environment.

In order to ensure that the patient sample remains representative of the cases that undergo treatment through National Health Service Child and Adolescent Mental Health Services (NHS CAMHS), no further exclusions are made.

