## Discussion

An important challenge to adolescent mental health services is the provision of appropriate and effective treatment to adolescents in need at the earliest possible point in time. To overcome this challenge, accuracy in both diagnostic assessment and prognostic evaluation of patients are critical, but as yet clinicians possess no objective tools for either. Diagnostic assessments rely on subjective retrospective information transmission from patient and/or parent to clinician whereas potential prognostic indicators of treatment outcome, such as depressive symptom severity or suicidal tendencies, are poor [43]. Therefore the overall aim of MR-IMPACT is to identify and evaluate objective neurobiological markers of depressive illness in adolescence and prognostic indicators of recovery following psychological treatment for depression.

Neural markers of depression in adolescence will be characterized by comparing structural and functional differences in patients with MDD prior to treatment against a group of healthy adolescent participants matched for demographic characteristics such as age, sex and IQ. Treatment-related changes will be identified by measuring changes in brain functional activation and connectivity prior to treatment and following at least six attended sessions of CBT. A placebo-controlled trial would have been an optimal method for assessing treatment-related changes, but impossible due to ethical constraints. Therefore, changes in brain function in healthy adolescents will also be measured at a second time point matched in length to that of the depressed group to ensure that functional changes indicative of adolescent development are not misidentified as changes related to CBT treatment.

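### The baseline patient-control contrast cannot by itself separate depression from comorbid disorder, yet the Discussion presents it as characterizing neural markers of depression

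*Protocol article*

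**What the plan says.** **Patients.** The Protocol article requires "Current DSM-IV unipolar MDD diagnoses with moderate to severe impairment determined by child and parent interviews using the K-SADS-PL". Its Exclusion criteria section lists three psychiatric or developmental grounds for exclusion: "Alcohol dependence", drug dependence, and "Pervasive developmental disorder or generalized learning problem". The remaining grounds concern pregnancy or breastfeeding, interacting medication and MRI suitability. The section closes by saying that, to keep the sample representative of cases treated through the "National Health Service Child and Adolescent Mental Health Services (NHS CAMHS), no further exclusions are made". Study participants adds: "Patients with chronic or recurrent MDD are also included, as are patients already taking antidepressant medication".

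**Controls.** At the home visit described under Study participants, "Screening for personal and family history of psychiatric illness and MRI contraindication will then be conducted". They are also screened for suicide attempts, suicidal thoughts and cutting, and those found eligible are scanned. Matching is on age, sex, IQ and handedness.

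**Analysis.** The first objective under Aims compares patients with healthy adolescents at baseline. The sMRI and fMRI data analysis plans look for between-group differences across the whole brain and in chosen regions, among them the amygdala.

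**Interpretation.** The Discussion states: "Neural markers of depression in adolescence will be characterized by comparing structural and functional differences in patients with MDD prior to treatment" with those of the matched healthy group. It gives the overall aim as "to identify and evaluate objective neurobiological markers of depressive illness in adolescence", together with prognostic indicators of recovery. The limitations paragraph deals with telling markers of illness from indicators of general non-response to treatment. It does not mention comorbidity.

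**The concern.** Under these criteria a patient with depression plus an anxiety, conduct, eating, obsessive or trauma disorder is included, while controls are screened for psychiatric history. The two groups can therefore differ in depression and in every retained comorbid disorder at once, and matching on age, sex, IQ and handedness removes none of the second difference. Existing antidepressant use among patients and family-history screening among controls add to the same lack of specificity.

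The inclusive sample is not the fault. It suits a study nested in a pragmatic trial. The trouble is the inference: the contrast estimates the combined effect of depression and its usual companions, and the Discussion attaches it to depression without qualification. A regional difference that arose wholly from, say, comorbid anxiety could be reported as a marker of depressive illness, which bears directly on the study's stated overall aim.

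**Working it through.** The article states no sample size, power or effect for the baseline contrast, so there is no figure of its own to reproduce. The check has two parts.

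**1. What the contrast can identify.** Let *D* be the mean shift due to depression, *p* the share of patients with a retained comorbid disorder (taken as 0 in controls) and *c* the shift due to that disorder, all in within-group SD units. The expected patient-control difference is *D* + *p* × *c*. A single contrast of all patients with controls gives one number, so *D* and *p* × *c* cannot be separated from it.

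**2. How large *p* × *c* might be.**

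- From the article: 120 patients (Study participants) and 40 controls (Sample size and power calculations, where the 40 is given for the CBT comparison).
- Assumed: *p* from 30% to 70%, *c* from 0.3 to 0.5 SD, *D* = 0, SD 1 in both groups.
- Standard error: √(1/120 + 1/40) = 0.183 SD.
- Rejection chance at critical value *z*: Φ(shift/SE − *z*) + Φ(−shift/SE − *z*), with *z* = 1.96 at two-sided 5% and 3.29 at two-sided 0.001.

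| Share × effect | Shift (SD) | Shift/SE | Rejects at 5%, uncorrected | Rejects at 0.001 |
|---|---|---|---|---|
| 0.3 × 0.3 | 0.09 | 0.49 | 7.8% | 0.3% |
| 0.5 × 0.5 | 0.25 | 1.37 | 28% | 2.7% |
| 0.7 × 0.5 | 0.35 | 1.92 | 48% | 8.5% |

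The two right-hand columns differ only in the strictness of the test. The bias in the estimate, 0.09 to 0.35 SD, is the same in both. A wider assumed range (shares 20-60%, effects 0.3-0.8 SD, allowing for the extra variance among patients) gives shifts of 0.06-0.48 SD, with rejection in 6-73% of studies at 5% and 0.2-24% at 0.001.

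**3. Precision of a comorbidity-free contrast.**

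- Half of patients qualify: √(1/60 + 1/40) = 0.204; 0.204/0.183 = 1.12, so 12% wider.
- 30% qualify (36 patients): √(1/36 + 1/40) = 0.230; 0.230/0.183 = 1.26, so 26% wider.
- If the true depression effect were 0.5 SD (assumed), power with 36 rather than 120 patients falls from 78% to 59% at 5%, and from 29% to 13% at 0.001.

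**The case against.** The strongest reply is that this is a condensed article. Its analysis sections name no covariates at all, so silence on a comorbidity analysis may only mean that the detail sits in a fuller document. That stands as far as it goes: a missing covariate list is no finding. It does not dispose of the point, which rests on what the article does state, namely the eligibility asymmetry, the contrast and the conclusion drawn from it.

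A second reply is that the inclusive sample is deliberate and justified, and that the first objective is descriptive. Both are true, and the fix leaves both alone. Representativeness supports a statement about clinic-referred depression; it does not support one about depression apart from its comorbidity. The Background does acknowledge heterogeneity, in mixed MDD subtypes and variable cases, but does not carry this over to the study's own case-control contrast.

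Three stronger readings are tempting and should not be drawn:

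- *That the plan will label every difference a marker of depression.* The Discussion says only that markers will be characterized by this comparison.
- *That controls are free of any disorder whatever.* The text says that they are screened and that eligible ones go on; exclusion for a positive history is implied, with no threshold given.
- *That the study cannot address the question.* The limit applies to the planned contrast. K-SADS-PL interviews are done for eligibility and trait anxiety is collected at the scan visit, so the data may well allow it.

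It is also fair that 8-48% comes from an uncorrected 5% test. The plan corrects for multiple comparisons and uses 0.001 in its whole-brain power calculation for predictors; at that level the same shifts give about 0.3-8.5%.

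**Conclusion.** The point holds as a mismatch between design and stated interpretation. The baseline contrast, taken alone, identifies differences between depressed clinic patients with their retained comorbidity and screened controls. It does not identify differences attributable to depression itself, and the Discussion neither qualifies the claim nor lists the limit.

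The size is not established. A shift of 0.09-0.35 SD depends on assumed comorbidity shares and effects, a zero depression effect and no comorbidity in controls. The rejection chances also depend on the test level and on taking 40 controls from another comparison. The direction of the argument needs none of these figures.

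This should be corrected, but it does not invalidate the data or the main contrast. The fault lies in the strength of the inference.

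**What to change.** 1. Keep the inclusive sample and the main contrast. Describe its differences as features of clinic-referred adolescent depression with its usual comorbidity, and add the limit to the limitations paragraph.
2. Prespecify a sensitivity contrast of controls against patients with no other current K-SADS-PL diagnosis. This assumes that those diagnoses are recorded and kept.
3. Prespecify a within-patient contrast of those with against those without comorbidity.
4. Judge specificity by setting effect estimates and confidence intervals side by side across the contrasts. Do not make it depend on whether significance persists in the smaller subset: that would read lost power as lost specificity.
5. State that comorbidity-free patients may be less severely depressed, so a smaller difference among them would not by itself show that comorbidity caused the rest.

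**Cost.** Two extra contrasts on data that should already be held, plus rewording. No new scans or recruitment are needed. The price is the lower precision of the restricted contrast shown in the working, which grows as fewer patients qualify.
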